### Description of the Intervention

ARAMIS is composed of two computer-controlled, symmetric, and interacting exoskeletons able to compensate for the inadequate strength and accuracy of residual motor function of the paretic arm movements (25) (Figure 1). Through motion capture of the movements of the unaffected arm, the patient can replicate the movements of the healthy arm with the paretic arm in a synchronous, asynchronous, or active-assisted manner (25). Patients in the intervention group will receive only robot-aided and not conventional rehabilitation for a 60 min-session. The robot-assisted neurorehabilitation using ARAMIS and the conventional rehabilitation consists of 60-min sessions every day for 8 weeks (17, 25). In particular, in the first section of neurorehabilitation (1–4 weeks), all the subjects will be subjected to perform a series of asynchronous exercises according to which the paretic limb repeats each exercise 20 times for a total of 200 repetitions per session. During synchronous exercises, the exoskeleton hosting the paretic limb allows the replication of the sample movements of the parallel exoskeleton hosting the unaffected arm in real time. In the asynchronous exercises, the sample movements have been generated previously by the unaffected arm of the patient or by the arm of the therapist. The basic exercises consist in forearm pronation-supination, elbow flexion-extension, shoulder elevation (30°, 60°, and 90°) and abduction-adduction (30°, 60°, and 80°), and circle movement on the frontal axis of the shoulder and its flexion-extension. On the other side, the functional exercise includes: shoulder elevation 90° + forearm pronation-supination and elbow flexion-extension and the contrary (elbow flexion-extension + forearm pronation-supination); shoulder elevation 90° + two elbow intermediate flexion-extension + forearm intermediate pronation-supination. In the following section (5–8 weeks), the asynchronous exercises are reduced to 100 per session and the number of synchronous exercises is increased to keep constant the total number (200/session). The control group will receive conventional rehabilitation. The latter consists of passive mobilization, neuromotor facilitation of shoulder, arm, forearm, and hand muscles and adoption of postures inhibiting pathological synergies in the first 4 weeks. In the following 4 weeks apart from a passive mobilization, neuromotor facilitation, and posture adopting, also the following exercises will be performed: coordination proximal-distal and of ocular-cephalic movements; “reach to indicate”; hand preconfiguration; “reach, touch, and manipulate”; grasping; exercises for manipulative skills, for the adaptation of the hand to the object without visual feedback and the sensitivity, together with biofeedback and electrostimulation cardiovascular conditioning in the sitting posture, conditioning in the upright posture and exercises for the trunk control.

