
**Figure 1 F1:**
[figure not shown]
Integrated Robotic System for Stroke (IRSS) prototype Automatic Recovery Arm Motility Integrated System (ARAMIS) [reproduced with permission from Pignolo et al. (25)].

In case of discontinuation of the treatment, the patient will be excluded from the study. The treatment will be performed by healthcare operators preventing lack of adherence.

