### Statistical Analysis

The statistical analysis plan follows the Consolidated Standards of Reporting Trials (CONSORT) evidence-based reporting guideline to ensure research transparency, specifically to trials of nonpharmacologic treatments (NPTs), as rehabilitation (48). The primary (pain) and secondary (spasticity and rehabilitation parameters) outcome measures, collected at prespecified time point *t*_3_ and *t*_4_ vs. *t*_0_, will be expressed as mean and standard error and assessed for statistically significant differences using independent *t*-test for data normally distributed or Mann–Whitney U test for skewed data. Based on the CONSORT NPT item 12b, the evaluation of the outcome measures over time will be carried out through a linear mixed model. The correlation between pain (VAS measure) and recovery (FMA-UE), assessed at *t*_0_, *t*_1_, *t*_2_, *t*_3_, and *t*_4_, will be performed through the Pearson product-moment correlation coefficient (*r*). In agreement with the CONSORT NPT item 12a, the clustering of data will be performed by blinded care providers of the center. Statistical analysis will be performed using SPSS statistics software (Chicago, IL, USA). Values of *p* < 0.05 will be considered statistically significant.

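### The clustering sentence assigns an analysis problem to care providers and calls them blinded; the stated arm comparisons make no allowance for shared therapists

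*Protocol article*

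**What the plan says.** The Statistical Analysis section cites a reporting item for non-drug trials ("In agreement with the CONSORT NPT item 12a") and then states that "the clustering of data will be performed by blinded care providers of the center". In the same section the arms are compared at 3 and 6 months against baseline by "independent *t*-test for data normally distributed or Mann–Whitney U test for skewed data". Separately, "the evaluation of the outcome measures over time will be carried out through a linear mixed model"; the terms of that model are not listed.

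On delivery, Description of the Intervention gives the control arm "passive mobilization, neuromotor facilitation of shoulder, arm, forearm, and hand muscles and adoption of postures inhibiting pathological synergies" in the first four weeks, with further exercises added later. For the other arm, "Patients in the intervention group will receive only robot-aided and not conventional rehabilitation for a 60 min-session". That section ends with "The treatment will be performed by healthcare operators preventing lack of adherence". It gives neither the number of operators nor whether they work in one arm or both.

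The section on recruitment, allocation, concealment and blinding provides blinding for data managers and biostatisticians. It does not mention care providers as blinded.

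**The concern.** Two things are wrong in the sentence itself. First, it treats clustering as an activity. In a therapist-delivered trial, clustering means that patients of one therapist tend to have more similar outcomes than patients of different therapists. That is a property of the data, dealt with by a model term or a justified decision to leave it out. Second, it calls care providers blinded, although the two arms look entirely different to anyone delivering them.

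As a result, the only sentence that raises clustering says nothing usable about how it is handled, and the two named arm comparisons assume independent patients. Depending on who treats whom, their standard errors may be too small. Read literally, the sentence also gives care providers a data step, which sits badly with the blinding arrangements elsewhere in the article.

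**Working it through.** **The wording, section by section**

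- Statistical Analysis: care providers are blinded and perform the clustering.
- Description of the Intervention: operators deliver either robot-only sessions or conventional therapy, so whoever treats a patient knows the arm.
- Blinding section: data managers and biostatisticians are blinded; care providers are not listed.

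The first statement cannot be reconciled with the other two if care providers means the treating staff. If other staff were meant, the article does not say so, and the sentence still describes no handling of clustering.

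**The plan's own sample size**

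The dropout step reproduces: 53/(1 − 0.10) = 58.9, so 59 per arm and 118 in total. The 53 itself cannot be reproduced, because no standard deviation is given. With the stated difference 6.34 − 5.4 = 0.94, it needs σ = √(53 × 0.94² / (2 × 2.80²)) ≈ 1.73. That is a separate matter. Here 53 per arm is taken as given; the formula contains no clustering allowance.

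**Effect on the 5% error**

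From the article: 53 analysed per arm, two-sided 5% (1.96). Assumed, because the article gives none of them: k therapists per arm, different in each arm; one main therapist per patient; ICC.

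- Patients per therapist: m = 53/k.
- Design effect: DE = 1 + (m − 1) × ICC.
- Variance ratio: DE if both arms are clustered, (1 + DE)/2 if only the conventional arm is.
- True error of the unadjusted test: 2 × [1 − Φ(1.96/√ratio)].

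With k = 4, m = 13.25:

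- ICC 0.02: DE = 1 + 12.25 × 0.02 = 1.245. Both arms: 1.96/√1.245 = 1.757, error 7.9%. Conventional arm only: ratio 1.1225, 1.96/√1.1225 = 1.850, error 6.4%.
- ICC 0.05: DE = 1 + 12.25 × 0.05 = 1.6125. Both arms: 1.96/√1.6125 = 1.543, error 12.3%. Conventional arm only: ratio 1.306, 1.96/√1.306 = 1.715, error 8.6%.

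True error with both arms clustered, over a wider range:

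| Therapists per arm | ICC 0.01 | 0.02 | 0.05 | 0.10 |
|---|---|---|---|---|
| 2 | 8.0% | 11.1% | 19.4% | 29.8% |
| 3 | 7.0% | 9.0% | 14.8% | 23.0% |
| 4 | 6.4% | 7.9% | 12.3% | 18.9% |
| 6 | 5.9% | 6.8% | 9.7% | 14.2% |
| 10 | 5.5% | 6.0% | 7.5% | 10.1% |

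**Simulation check** (20,000 trials per setting)

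- Therapists nested in arm, k = 4, ICC 0.05: 12.6%, against 12.3% by formula.
- The same therapists spread evenly over both arms, with the same effect in each (k = 4 or 6, ICC 0.02 to 0.10): 4.0% to 4.8%. The therapist effect cancels in the contrast, so there is no inflation.

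**The case against.** A reader might infer that therapist differences are in fact mixed into the robot effect and that the standard errors are in fact too narrow. The article does not support that. It requires an ICC above zero, a main therapist for each patient, and either staff who work in one arm only or an effect that acts mainly in one arm. None of these is stated. With daily sessions over 8 weeks, a patient may well see several staff, which would blur the clusters. The evenly crossed case shows that the error can stay at or below 5%.

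A reader might also infer that therapists who know the arm will process outcome data. The sentence speaks of providers of the center, not expressly of those who treated trial patients, and the blinding section points to separated roles and double data entry by independent operators. The supportable charge is wording that conflicts with those arrangements.

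Nor is it a finding that no therapist term is named for the mixed model. A condensed article commonly leaves such detail to the full protocol or the SAP, and nothing here rules the term out. The text of the cited reporting item is not in the article either, so the sentence can be judged only on its own content. Finally, the trial describes itself as a pilot and exploratory, which lowers the weight of a possible excess in the 5% error.

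All of this stands, with one limit. Sharing staff across arms protects the test only if the therapist matters equally in both. If therapist skill counts mainly in hands-on therapy, crossing does not cancel it, and the conventional-arm-only figures apply. Some therapist influence in the robot arm is possible too, since sample movements may be "generated previously by the unaffected arm of the patient or by the arm of the therapist". None of the objections rescues the sentence: a model term in an unseen document would leave it just as wrong.

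**Conclusion.** The sentence is wrong as written and should be replaced. That conclusion rests on the article's own text and needs no assumption about therapists.

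The effect on inference is conditional. For 4 therapists per arm, one main therapist per patient and ICC 0.02 to 0.05, the nominal 5% becomes about 8% to 12% with both arms clustered and about 6% to 9% with the conventional arm only. With the same staff treating both arms evenly and a common effect, it stays at about 4% to 5%. The article gives neither the staffing nor an ICC, so it cannot be said which case applies.

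**What to change.** Replace the sentence in Statistical Analysis with:

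*The main treating therapist is recorded for each patient, and which staff treat which arm is stated. Clustering by therapist is addressed in the linear mixed model by a therapist effect with small-sample degrees of freedom, reported beside the unadjusted comparison. Outcome data are prepared only by the blinded data managers; care providers take no part.*

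The therapist should be recorded prospectively, since the information may not be recoverable later.

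The cost is one extra case report form field and an adjusted interval that may be noticeably wider and imprecisely estimated with few therapists. For example, with 4 nested therapists per arm the degrees of freedom could be about 2 × (4 − 1) = 6, giving a critical value of about 2.45 instead of 1.98. With the standard error multiplied by √1.6125 = 1.27 (ICC 0.05), the interval is about 1.27 × 2.45/1.98 = 1.57 times as wide. For that reason the adjusted result is best reported beside the unadjusted comparison and not as the only estimate.

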**Methods:**

A total of 118 patients with hemiplegic arms due to stroke will be enrolled and randomly allocated with a 1:1 ratio to ARAMIS or conventional neurorehabilitation group. After a baseline screening at hospital discharge, ARAMIS or conventional rehabilitation will be performed for 8 weeks. The primary endpoint is the prevention of the development of poststroke pain and the secondary endpoints are prevention of spasticity and efficacy in clinical motor rehabilitation. The primary outcome measures consist in the visual analog scale and the doleur neuropatique 4 and the secondary outcome measures include: the Modified Ashworth Scale, the Resistance to Passive movement Scale; the Upper Extremity Subscale of the Fugl–Meyer Motor Assessment; the Action Research Arm Test; the Barthel Index for activities of daily living; and the magnetic resonance imaging (MRI) recovery-related parameters. After baseline, both primary and secondary outcome measures will be performed in the following time points: 1 month after stroke (*t*_1_, half of the rehabilitation); 2 months after stroke (*t*_2_, after rehabilitation); and 3 months (*t*_3_) and 6 months (*t*_4_) after stroke, critical for poststroke pain development.

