### Outcomes

The effect of robot-assisted rehabilitation using ARAMIS on the prevention of the development of poststroke pain is the primary endpoint of the ROBOCOP study. The primary outcome measures consist in the assessment of pain through the VAS, including a bedside active examination and probing of somatosensory functions to test touch, temperature, and pain sensations (26). The development of neuropathic components of poststroke pain will be assessed using the DN4. The secondary endpoints include spasticity, tightly linked to pain and developed by up to 40% of patients with hemiparetic stroke, and clinical motor rehabilitation. Spasticity will be assessed using the Modified Ashworth Scale (MAS) (27) and the Resistance to Passive movement Scale (REPAS), based on the Ashworth scale (28), for major joint movements in upper and lower limbs. Clinical motor rehabilitation will be measured according to the Standardizing Measurement in Arm Rehabilitation Trials [SMART] toolbox of the recommended core set of outcome measures for rehabilitation after stroke (29, 30). The latter includes FMA-UE, the Action Research Arm Test, and the activities of daily living/stroke-specific outcomes of the Barthel Index. The clinical motor rehabilitation will also be characterized through structural and functional MRI scan. In particular, structural MRI is intended to evaluate infarct and injury volume (31) and functional MRI to assess the activation volume in the stroke ipsilateral hemisphere during movement of paretic limb, which is related to the extent of behavioral recovery (32). The connection strength between the ipsilesional primary motor cortex and the contralateral regions will be examined (33).

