### Sample Size

The calculation of the sample power is based on literature data (25, 36–40) to obtain 25% of improvement in the primary endpoint using G^*^Power 3.1.9.7 (41). The formula for calculating the sample size is given, for two arms of the same size, as it follows:

$$\begin{array}{l} n=\left[{\left(Z_{\alpha /2}+Z_{\beta }\right)}^{2}\times \left(2{\left(\sigma \right)}^{2}\right)\right]/{\left(\mu 1-\mu 2\right)}^{2} \end{array}$$

where,

*n* = sample size required in each group;

*Z*_α/2_ = 1.96, according to 5% level of significance;

*Z*_β_ = 0.84 for 80% power;

σ = standard deviation;

μ1 – μ2 = primary outcome measures significant difference = 6.34 with ARAMIS and 5.4 with conventional rehabilitation (25);

*d* = 0.3.

Therefore, considering a 95% confidence level and a study power of 80% (42), the result will be *n* = 53 per arm.

Adjusted sample size *n*_1_ to account for potential drop-out rates is *n*_1_ = *n*/(1–*d*), where *d* = 10% (43), thus *n*_1_ = 118 patients will be recruited, 59 per each arm.

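### Two primary pain measures at two time points share one unadjusted 5% threshold and no comparison is named as deciding, while the sample size covers a single test

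*Protocol article*

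**What the plan says.** The Methods part of the Abstract names two primary measures: "The primary outcome measures consist in the visual analog scale and the doleur neuropatique 4". The Outcomes section presents VAS, with a bedside sensory examination, as the primary measure and then adds in a separate sentence: "The development of neuropathic components of poststroke pain will be assessed using the DN4". It does not state that DN4 ranks below VAS.

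The Statistical Analysis section covers primary and secondary measures together: "outcome measures, collected at prespecified time point *t*_3_ and *t*_4_ vs. *t*_0_, will be expressed as mean and standard error". The between-arm test is an "independent *t*-test for data normally distributed or Mann–Whitney U test for skewed data". The same section adds that "the evaluation of the outcome measures over time will be carried out through a linear mixed model", and it closes with one threshold for all of this: "Values of *p* < 0.05 will be considered statistically significant". Participant Timeline treats 3 and 6 months jointly as the key times for pain and puts neither first.

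The Sample Size section uses a normal quantile of "1.96, according to 5% level of significance", 80% power and one difference in means (6.34 against 5.4). It does not attribute that difference to VAS or DN4, or to a time point. Objectives calls the trial a pilot, and Trial Design calls it exploratory.

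**The concern.** A 5% significance level describes the primary claim only if one test decides it, or if a rule says how several tests combine. On the text as it stands, VAS at 3 months, VAS at 6 months, DN4 at 3 months and DN4 at 6 months can each be read as a primary result at 0.05, with a mixed model of the same outcomes beside them. The article gives no main measure, main time point, order of testing, all-must-succeed rule or adjustment.

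Two things are at stake. The measure or time point that happened to reach significance could be presented afterwards as the primary finding. And a sample size built for one test cannot guarantee both the stated error rate and the stated power for a claim that rests on several.

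**Working it through.** **Inputs from the article.** Primary measures: 2 (Abstract). Time points: 2 (Statistical Analysis). Threshold per test: 0.05. Sample size: two-sided 5%, 80% power, means 6.34 and 5.4, 53 per arm, 10% dropout, 59 per arm and 118 in total. Not given: the correlation between tests, the standard deviation and the success rule. These are varied or assumed below.

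**1. The plan's own figure.** The dropout step reproduces: 53 / (1 − 0.10) = 58.9, so 59 per arm and 118 in total. The 53 cannot be checked directly because no SD value is printed. Solving the article's formula for the SD gives σ = 0.94 × √[53 / (2 × (1.96 + 0.84)²)] = 0.94 × √(53 / 15.68) = 1.73, a standardised difference of 0.94 / 1.73 = 0.54. This back-solved SD is an assumption. The formula contains one comparison at 5%, with no allowance for more.

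**2. Error if any one significant result counts.** For k independent null tests the error is 1 − 0.95^k.
- k = 4: 1 − 0.95⁴ = 18.5%.
- k = 2: 1 − 0.95² = 9.75%.

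The tests share patients, so they are correlated. Simulating jointly normal test statistics under the null (2 million draws, equal correlation r between tests) gives:

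| r | Four tests (VAS and DN4, two times) | Two tests (VAS only, two times) |
|---|---|---|
| 0 | 18.5% | 9.8% |
| 0.3 | 17.4% | 9.5% |
| 0.5 | 15.6% | 9.1% |
| 0.7 | 13.0% | 8.3% |
| 0.8 | 11.4% | 7.8% |
| 0.9 | 9.4% | 7.0% |

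Every entry exceeds 5%.

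**3. Adding the mixed model.** The article does not say which contrast would be tested. As an illustration, one average-effect contrast over t1 to t4 per measure was added to the four tests. With correlation 0.3 to 0.9 between times and 0 to 0.7 between measures, the any-one error becomes about 12% to 22% (18.7% when both are 0.5, against 16.1% for the four tests alone).

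**4. If all tests must succeed.** The error under the null is then at most 5%. If each test has 80% power, joint power is 0.8⁴ = 41% for four independent tests and 0.8² = 64% for two. It rises to 80% only with perfect correlation.

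**5. If several tests stay primary with adjustment.** With difference 0.94, SD 1.73 and 53 per arm:
- Four tests at 0.05 / 4 = 0.0125: error 1 − 0.9875⁴ = 4.9% if independent. Power per test is about 62%. Restoring 80% needs 76 per arm, and 76 / 0.9 = 84.4, so 85 after dropout.
- Two tests at 0.05 / 2 = 0.025: power per test is about 71%. Restoring 80% needs 65 per arm, and 65 / 0.9 = 72.2, so 73 after dropout.

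**The case against.** Four arguments can be made for the plan.

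**It is an exploratory pilot.** Strict familywise control is mainly expected of confirmatory trials, and the article never claims confirmatory status for DN4 or the 3-month result. This stands as a reason to call the consequence moderate. It does not settle the matter, because the article still declares a primary endpoint, a 5% level and 80% power.

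**Four primary tests is only one reading.** The Outcomes section leads with VAS and gives DN4 the neuropathic component, and the Statistical Analysis section does not mention DN4 by name. This is fair, and it is why the VAS-only case is shown. Two time points still give about 7% to 10%.

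**The inflation is conditional.** A reader might infer that the trial's false-positive rate simply is 18.5%, or somewhere in the teens. The article does not support that. The figure requires that any single significant result counts as success, which is nowhere stated, and the upper end requires independence, which is not credible for two pain tools used in the same patients. The article likewise does not present the mixed model as a further deciding test, so the 22% figure is an illustration only.

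**A fuller plan may hold the hierarchy.** It may, and a reader should not infer that none exists. The point rests on what the article does fix: one unadjusted threshold for all tests, beside a sample size for one.

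**Conclusion.** The point holds in conditional form. As written, the 5% level and 80% power cannot both be properties of the primary claim, unless the tests are perfectly correlated.

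- Any one result suffices: false-positive chance about 9% to 19% with four tests, or about 7% to 10% with VAS alone at two times. Both ranges assume correlation from 0.9 down to 0.
- All results are required: no inflation, but power below 80%.

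Which case applies cannot be told from the article, and that is the defect. For a self-described exploratory pilot the consequence is moderate, but the correction is cheap and should be made.

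**What to change.** Before unblinding, name one deciding comparison as a difference in means, which is the form used in the sample size. An example is the between-arm difference in mean VAS at one of the two time points, such as 6 months, tested at two-sided 0.05. The choice between 3 and 6 months belongs to the investigators. Make the other time point and DN4 secondary, or test them in a stated fixed order only after the deciding comparison succeeds. Label the mixed model supportive.

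This takes a sentence or two in the Statistical Analysis section and no extra patients. The price is that DN4 and the other time point can no longer carry the primary claim on their own. Redefining the endpoint as presence or absence of pain would be a different change and would need a new sample size.

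If several tests must remain primary, apply Holm and restate the power. With four tests, its first step is the Bonferroni level of 0.0125, where 53 per arm gives about 62% power per test under the back-solved SD of 1.73.
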